### Outcome measures

These are detailed in table 4. The proposed primary outcome for the main trial is the BRIEF-2,^34^ a parent and self-report measure of everyday executive function skills. Secondary outcomes will include parent reports of their child’s health and behaviour, using the Revised Child Anxiety and Depression Scale^37^ (RCADS) and Strengths and Difficulties Questionnaire^38^ (SDQ) to evaluate the adolescents’ social, emotional and behavioural functioning.

**Table 4 T4:** Trial schedule

Study procedure	Screening	Baseline		Follow-up **17** weeks
Consent/assent (adolescent+/-parents)	X		16 week intervention period	
Consent (parents)	X			
Characteristics of ABI (CRF)	X			
Current medication (adolescent)		X		X
BRIEF parent-rating	X			X
Parents				
Demographics, past medical history		X		
SDQ parent-rated		X		X
PHQ-9		X		X
GAD-7		X		X
CBQ		X		X
EQ-5D-5L		X		X
CSRI		X		X
RCADS parent version		X		X
Adolescents				
Consent/assent (participants+/-parents)	X			
BRIEF-2		X		X
RCADS		X		X
SDQ		X		X
CHU-9D		X		X
CBQ		X		X
Both parent and adolescent				
Treatment adherence				X
Treatment acceptability rating				X
Study participation feedback				X
Qualitative telephone interviews (all)				X

ABI, acquired brain injury; CBQ, Conflict Behaviour Questionnaire; CHU-9D, Child Health Utility 9D; CRF, case report form; CSRI, Client Service Receipt Inventory; BRIEF-2, Behaviour Rating Inventory of Executive Function, Second Edition; EQ-5D-5L, EuroQol 5 Dimensions 5 Levels Questionnaire; GAD7, Generalised Anxiety Disorder 7-item; PHQ-9, Patient Health Questionnaire 9; RCADS, Revised Child Anxiety and Depression Scale; SDQ, Strengths and Difficulties Questionnaire.

A mixed methods approach (questionnaires and interviews) will be used to address outcomes relating to adolescent and parent acceptability of the intervention and outcome measures, coach’s experience of supporting intervention delivery, parents’ and adolescents’ experiences of study participation, assessment of participants’ willingness to be randomised to treatment and complete outcome measures, evaluation of appropriateness of the trial and economic evaluation methods and procedures and adolescent and parent experiences of TAU (TAU arm).

Parental reports of their own and family quality of life, health, emotional functioning and family interactions will be evaluated using the EuroQol 5 Dimensions 5 Levels questionnaire^39^ (EQ5D-5L), the Patient Health Questionnaire^40^ (PHQ-9), the Generalised Anxiety Disorder^41^ (GAD-7) questionnaire and the Conflict Behaviour Questionnaire^42^ (CBQ).

Use of health and social care resources will be assessed through parental report on the Modified Client Service Receipt Inventory^43^ (CSRI). Adolescents involved in the study will also complete questionnaires relating to their executive function skills (BRIEF-2^34^ adolescent version), quality of life (Child health-related quality of life^44^; CHU-9D), emotional functioning (RCADS),^37^ social, emotional and behaviour functioning (SDQ)^38^ and their family interactions (CBQ).^42^

The EQ-5D-5L and CHU-9D also provide data on quality-adjusted life-years (QALYs) which can be used in cost-effectiveness analyses.

### Follow-up questionnaires

Adolescents and their parents in both treatment arms will be sent an email asking them to complete their online follow-up outcome measures at 17 weeks post-randomisation. In the event of non-completion, at least two reminders will be sent by email, followed by a reminder telephone call from the site research team if required. As with the baseline measures, participants will be given the option (at consent/assent) to complete the online follow-up measures with telephone support from a member of the research team. If participants do not complete the follow-up measures within 4 weeks they will receive a ‘last chance’ email with a reminder of the study link. A £15 gift voucher will be sent to each family following completion of the follow-up questionnaires.

It is acknowledged that a definitive trial would require longer follow-up than this feasibility study will provide, but the feasibility trial will inform the acceptability of outcome measures and the experience of participating in the trial. The power calculation for a definitive trial with longer follow-up will account for a higher level of attrition than this feasibility trial.

## Qualitative interviews

A single qualitative researcher will conduct semi-structured qualitative process evaluation interviews by telephone or video call with all participants (including those who have not completed follow-up questionnaires but who have not formally withdrawn from the study), research nurses and the study coach. PIS relating to the qualitative interviews will be emailed in advance and consent will be sought at the beginning of the interview by the qualitative researcher. Adolescent and parent participants will be offered the option of being interviewed together or separately. Interviews will be conducted with the help of an agreed topic guide (see online supplementary appendix) and are expected to last between 20 to 60 min. Interviews will be audio-recorded and transcribed verbatim. The transcribed interview data will be fully anonymised and any demographic data about participants will be stored separately. Qualitative interview data will be managed using a computer software package such as Nvivo 11 and thematically analysed.^45^ The analysis and results will be checked/validated by a second qualitative researcher. The following interviews will be conducted:
**All participants** (both groups). These interviews will allow participants to describe their whole experience of participating in the study including their willingness to be randomised and their experiences and acceptability of outcome measures, what worked well and what less well. This will cover aspects such as clarity of PIS, acceptability and ease of completing the online consent process, ease of completing online questionnaires and the parental support required the adolescent to participate and remain engaged. The interviews will explore adolescent and parent experiences of TAU or TAU + TOPS-UK, including parent’s perceptions of the impact of TAU/TAU + TOPS-UK on their ability to support the adolescent, adolescent’s and parent’s perceptions of the impact of TAU/TAU + TOPS-UK on adolescent’s ability to stay positive, solve problems, be organised, control their emotions and look after themselves (self-care), and participants’ views on potential improvements to TAU/TAU + TOPS-UK. In addition, participants in the TAU + TOPS-UK will be asked about their experience of working with the coach via video calls. This information will be helpful when planning the full RCT and implementation studies. After completion of the interview, each family will be sent a £15 gift voucher as a token of appreciation.
**Interview with TOPS-UK coach**. A single interview will explore the coach’s experiences of supporting the TOPS-UK intervention. The interview will be held by telephone, or face-to-face, once every participant allocated to the intervention arm has completed the programme.
**Interviews with research nurses.** All research nurses involved with the study at the five participating sites will be invited to participate in a single interview to explore their experiences of supporting families through the consent process and any support required to complete baseline or follow-up measures. Feedback on methods of contact with families, number of contact attempts made, how much support was required from adolescents and/or parents, barriers to recruitment and suggestions for future studies will also be sought.

10.1136/bmjopen-2019-029349.supp1Supplementary file 1

Participants who withdraw from the study, participants who register their interest but do not complete the study consent forms and participants who discontinue the intervention and who do not complete the follow-up questionnaires (ie, non-adherent but not explicitly withdrawn), will be invited to complete an anonymous online feedback survey. The survey will invite participants to comment on any aspects of the study that they found difficult, any aspects of the study that they liked and suggestions on how the study can be improved.

## Economic evaluation

This feasibility study will be used to develop a framework for a subsequent, policy-relevant, cost-effectiveness analysis to be undertaken alongside a future RCT. Economic evaluation methods will be developed and assessed regarding the collection of resource use, cost and outcome data. Data on resource use associated with the set-up and delivery of the TOPS treatment will be collected at the participant and coach level for example, coach contact and non-contact time per participant, equipment and consumable costs, training and supervision requirements for the TOPS-UK coach. Data regarding service use will be collected from all participants’ parents using a version of the CSRI specifically modified for this population. This includes use of mental health, community rehabilitation and neuropsychology and educational psychology services and has been previously trailed in this population (Wilson *et al*, in preparation). In addition to informing the development of the economic evaluation methods, this will provide a profile of the resources and services that constitute TAU. The study will also consider the most appropriate manner in which to capture data on health-related quality of life for use in the estimation of the cost per QALY of the TOPS-UK treatment. The feasibility of participants self-completing the CHU-9D and parents completing the EQ-5D-5L, will be assessed.

In addition to this primary economic outcome, the appropriateness of considering the cost-per unit change on other relevant indicators of health status collected in the baseline and follow-up phases will be explored.

## Safety reporting

The risks associated with participating in this study are considered minimal. There is a slight chance for those in the intervention group that raising awareness of injury-related cognitive or behavioural problems through communication and problem-solving might increase family burden and possibly contribute to conflict between family members. However, the purpose of the intervention is ultimately to equip families with skills to handle these difficulties by learning how to change the way they solve problems and talk with one another, and the TOPS-UK coach supporting the online intervention will be trained to handle any emerging problems. Should any issues arise, the coach will have access to a qualified clinical psychologist to provide further support and advice. There is therefore no requirement to report non-serious adverse events in this study, although serious adverse events (SAEs) will be monitored.

SAEs may be reported by clinicians or researchers at site, the TOPS-UK coach, by participants themselves or by any other informant. Adverse event data will be monitored by the Trial Steering Committee (TSC) to ensure safety. The TSC includes an independent statistician, psychologist, paediatrician and patient and public representative and will meet on approximately four occasions. All suspected SAEs will be reported within 24 hours of discovery to the CTU who will notify the Chief Investigator. All SAEs will be followed up until resolution.

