### Setting

Two settings will be utilised to examine feasibility outcomes associated with recruitment of adolescents known to have had a pABI:Direct referral by clinicians of adolescents who are under the outpatient care (usually neurology, neuropsychology or paediatric) of five participating NHS Trusts in England. Screening logs will be maintained at all sites to record the number of patients screened and enrolled in the study. These sites were selected to be representative of the range of types of services which might be included in a future trial, with TAU ranging from no provision through to services providing multidisciplinary outpatient care over the long-term.Recruitment from Participant Identification Centres (PICs) in primary or secondary care, or charitable organisations. Potential participants will respond directly to study promotion including leaflets/posters/participant information sheets distributed by parent-led groups, charities or support groups.

Study participation will be supported by research nurses at each participating NHS Trust. For participants directly referred to the study, nurses will make the first approach to the family. For those identified through PICs, families will be asked to contact the research nurse whose details are provided on the patient information sheet (PIS). The research nurse will support all families during the online consent and will be a point of contact for all participants during the study. The research nurse or other research team member will support baseline and follow-up measure completion. The intervention will be provided through online materials and video conference links with a coach trained in the TOPS-UK intervention. The coach will also receive weekly supervision from a qualified clinical psychologist on the research team to ensure treatment fidelity. The single study coach will be centrally based at the lead site.

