### Randomisation

Participants will be randomised via a web-based system created by the CTU in conjunction with the trial statistician, using minimisation by study site and type of brain injury (TBI/tumour/other). Participants will be randomly allocated in a 1:1 ratio to receive either TAU or TOPS-UK + TAU. The minimisation process will retain a stochastic element to retain allocation concealment. If any participant is found to be ineligible following randomisation, he/she will be excluded from analyses.

This study is not blinded. Following randomisation, the adolescent, parent, PI and research nurse will be notified by email of the adolescent’s treatment allocation, and this information will be held on the study site file. The parent and adolescent will also be advised when to expect further contact from the research team. In addition, the TOPS coach will be notified of all participants allocated to the intervention arm (TOPS-UK + TAU).

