### Teen online problem-solving (intervention)

TOPS is an online intervention, which is provided by the Cincinnati Children’s Hospital website, via a link from the study website. For the purposes of this study, the US-based TOPS treatment content was edited to include British (English) spelling, narration and UK resource links, and modified to suit participants with pABI rather than traumatic brain injury only. All participants allocated to the TAU + TOPS-UK arm will be supported by a single TOPS-UK coach who will make weekly contact by video conference.

For those participants allocated to TAU + TOPS-UK, the TOPS-UK coach will contact the parent and/or adolescent by telephone, introduce themselves, discuss how to access the treatment modules on the website and how to log in for subsequent video call sessions. The coach will email these participants a ‘start-up’ pack describing how to access the online materials.

Ten subsequent sessions (table 2) consisting of self-guided didactic content regarding problem-solving skills, video clips modelling these skills and exercises to practise the skills, will then be completed every 7 to 10 days by the family and the adolescent with pABI. The online modules should take 30 min to complete, with the video call sessions taking 60 min. The parent will work together with the adolescent to complete the sessions. When the family has reviewed the materials for each session, the TOPS-UK coach will conduct a video call with the adolescent and parent who agreed to participate in the study. During this session they will review the online materials and practise the problem-solving skills using a problem identified by the family/adolescent. They will then plan the next session and agree a suitable time for the video call. Ideally, video calls will be held weekly, but this period can be increased as agreed through discussions between the coach and the family.

**Table 2 T2:** TOPS-UK sessions (complete 10 in total)

Core sessions (complete all five)	Getting started and staying positive
	Steps of problem-solving
	Getting organised
	Staying in control
	Taking care of you
Tailored sessions (choose four)	Dealing with fatigue
	Managing fear and worry
	Controlling your anger and improving communication
	Listening, talking and reading non-verbal cues
	Social behaviour and joining a group
	Working with the school
Core final session	Bringing it all together

TOPS-UK, Teen Online Problem-Solving, British version.

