For all families allocated to TAU + TOPS-UK, the TOPS-UK coach will record details in the study database relating to intervention compliance for example, number and date of Skype sessions completed, length of each session, progress/engagement of adolescent and parent.

Completion of all 10 modules is expected to take each family 16 weeks in total. If the programme has not been completed after 16 weeks the intervention will be discontinued at that point. Study follow-up will proceed as if the programme had been completed.

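### SAE ascertainment is not standardised across arms: the coach, a named SAE reporter, meets intervention families only, and neither arm has a scheduled SAE enquiry

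*Protocol article*

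**What the plan says.** All from the protocol article:

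- **Routes for SAEs (Safety reporting).** "SAEs may be reported by clinicians or researchers at site, the TOPS-UK coach, by participants themselves or by any other informant". Suspected SAEs go to the trials unit within 24 hours of discovery, and the Trial Steering Committee (TSC) monitors adverse event data. Non-serious events are left out: "There is therefore no requirement to report non-serious adverse events in this study".
- **Coach contact (Teen online problem-solving).** "All participants allocated to the TAU + TOPS-UK arm will be supported by a single TOPS-UK coach who will make weekly contact by video conference". There is an introductory telephone call and then ten sessions. Weekly is described as the ideal, and the interval may be lengthened by agreement. On duration: "Completion of all 10 modules is expected to take each family 16 weeks in total". Under Randomisation, the coach is notified of intervention-arm participants; no coach role is given for TAU.
- **Contact in both arms.** Under Setting, the research nurse "will be a point of contact for all participants during the study". Under Follow-up questionnaires, adolescents and parents in both arms "will be sent an email asking them to complete their online follow-up outcome measures at 17 weeks post-randomisation". Non-completers get email reminders and, if required, a telephone call from the site team. Interviews are planned with all participants.
- **Schedule (Table 4).** Screening, baseline and 17 weeks. There is no adverse-event row. The service-use inventory (CSRI) and current medication are collected at baseline and 17 weeks.
- **Blinding and analysis.** The study is open-label. Analysis is descriptive, and no SAE comparison by arm is described.

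**The concern.** One of the named reporters exists in one arm only and talks to those families often. An admission or other serious event in an intervention family has up to eleven coach contacts in which it could come up. The same event in a TAU family has none before week 17, unless the family, the nurse or a treating clinician raises it. The Setting section says TAU ranges from no provision to long-term multidisciplinary care, so at some sites routine clinical contact may be sparse as well.

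The 24-hour rule does not help, because its clock starts at discovery. At equal true risk, more SAEs would tend to come to light in the TOPS-UK arm, while TAU events could go unseen. Two things are at stake. The first is how the TSC reads the safety data. The second is whether this study tests a usable safety procedure: objective 9 asks if the trial methods yield the information required.

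**Working it through.** The article states no SAE rate, SAE count or detection probability, so there is no figure to reproduce. The check has two parts.

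**1. Opportunities for detection, from the stated schedule**

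| Period | TAU + TOPS-UK | TAU |
|---|---|---|
| After allocation notice, to week 16 | 1 introductory call + 10 coach sessions = 11 contacts | none stated |
| Week 17 / end of trial | questionnaires (with CSRI and medication), interview | same |
| Unscheduled, throughout | site clinicians and researchers, research nurse, family | same |
| Scheduled SAE question | none | none |

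The arms differ only in the first row. The article does not say that the coach asks about SAEs, so the difference lies in the opportunity to learn of an event and not in active questioning.

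**2. Possible size (illustration only)**

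Inputs from the article: 25 participants randomised 1:1, so 12.5 per arm on average. Assumptions not in the article: the same true risk p in both arms (5%, 10% or 20% per participant), detection d = 1.0 in TOPS-UK, and d = 0.8 or 0.5 in TAU.

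- Expected SAEs seen per arm = 12.5 × p × d
- Apparent ratio = 1.0/d for TAU: 1.0/0.8 = 1.25, or 1.0/0.5 = 2.0
- Chance of seeing at least one affected TAU participant among 12 = 1 − (1 − p × d)^12

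| p | Seen, TOPS-UK | Seen, TAU (d = 0.8 / 0.5) | Gap | Chance of at least one seen in TAU (d = 1 / 0.8 / 0.5) |
|---|---|---|---|---|
| 5% | 0.62 | 0.50 / 0.31 | 0.12 / 0.31 | 0.46 / 0.39 / 0.26 |
| 10% | 1.25 | 1.00 / 0.62 | 0.25 / 0.62 | 0.72 / 0.63 / 0.46 |
| 20% | 2.50 | 2.00 / 1.25 | 0.50 / 1.25 | 0.93 / 0.88 / 0.72 |

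Example at p = 10%, d = 0.5: 12.5 × 0.10 × 0.5 = 0.62 events seen, and 1 − 0.95^12 = 0.46.

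The ratio depends entirely on the assumed detection. In absolute terms the gap is about one event or less, and 1.25 at the extreme of this range.

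**The case against.** **Shared routes exist.** Site clinicians and researchers may report in both arms, and a research nurse is available to every family. At week 17 both arms report service use and medication, and all participants are to be interviewed, including questionnaire non-completers who have not withdrawn. A reader might infer that TAU events surface only if a family volunteers them; the document does not support that. What remains is that none of these routes is named as an SAE enquiry, and the scheduled ones come only at the end.

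**The coach route is passive too.** A reader might infer that coach calls screen for SAEs. The article lists session dates, length, progress and engagement as examples of what the coach records, and no SAE question. This stands, and it limits the point to unequal opportunity.

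**No comparison by arm is planned.** The article describes case-by-case handling and a descriptive analysis. This also stands, so the concern applies to any count by arm that is later shown or read, not to a planned test.

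**The named harm is measured elsewhere.** Family conflict is the risk the article identifies, and the Conflict Behaviour Questionnaire (CBQ) is completed by parent and adolescent in both arms at baseline and 17 weeks, with between-group summaries planned. That answers any claim that this harm goes unseen because non-serious events are not reported.

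**An article condenses.** The full protocol may contain a standard SAE enquiry. If it does, the point is met. The reporting routes and schedule printed here, however, are unequal as they stand.

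**Conclusion.** The concern holds in limited form. On the stated routes, SAE ascertainment is not standardised: one arm has eleven scheduled contacts with a named SAE reporter, the other has none stated before week 17, and neither has a scheduled SAE question. TAU events are more likely to be missed, and SAE counts by arm are open to bias of unknown size.

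It would go too far to say that the counts are biased against TOPS-UK, or to attach a ratio to the bias. That needs detection probabilities the document does not give, and a comparison it does not describe. It is equally unsupported to say that a definitive trial would inherit the gap, since this study exists to test and revise procedures.

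With about 12 participants per arm the effect is probably around one event or less, assuming equal true risk of 5% to 20% and TAU detection of at least half that in TOPS-UK. This is a cheap improvement to a low-risk feasibility study and does not threaten its main aims.

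**What to change.** 1. Add one SAE question, identically worded in both arms and covering the period since randomisation, to the 17-week parent questionnaire. Ask the same question in the existing reminder telephone call to non-completers.
2. List every SAE with its source (common question, coach, site staff, family, other).
3. Base any summary by arm on the common question, giving the number of families who answered it in each arm; the article anticipates 20% loss to follow-up, about 5 of 25 (0.20 × 25). Otherwise, state that SAE counts by arm are not comparable.
4. Optionally, show the TSC the CBQ summary by arm, which is already planned.

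The cost is one more questionnaire item, one extra column in the SAE listing and possibly a few more SAE reports to process. The question is retrospective, so it supplements the 24-hour reporting route and does not replace it.
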